### **Quality control and assurance**

Internal standard operating procedures will be followed for the preparation, implementation, documentation, and the analyses of the clinical trial. All applicable regulations will be followed. The pharmacy of the University Hospital Heidelberg is holding a manufacturing license and is therefore authorized to produce the required study medication. Packing, labeling, and blinding will take place according to the applicable GCP and Good Manufacturing Practice regulations and standards.

As required by the German Drug Law (AMG) for multicenter trials, the sponsor has appointed a coordinating investigator (German: Leiter der klinischen Prüfung). Moreover, every trial site has appointed one principal investigator and at least one deputy investigator. All trial physicians and trial centers comply with the qualification requirements of the responsible Ethics Committee in terms of professional education, experience in clinical trials and equipment. Since the trial medication is well characterized, of low risk, and tested in a non-critical indication (fatigue), a Data Monitoring Committee has not been set up [37].

All data obtained in the course of the trial will be treated pursuant to the German Federal Data Protection Act (BDSG) and the European ordinance (EU) 2016/679. The individual participants will be exclusively identified by their patient identification and randomization numbers. The investigators will provide direct access to source data/documents for trial-related monitoring, audits, and regulatory inspection. Each participant will have to consent via written informed consent to direct access to their original medical records for trial-related monitoring, audit, and regulatory inspection.

Qualified staff will regularly monitor every study site by reviewing source documents, entries into the eCRFs, and essential documents to ensure that the trial complies with the protocol and regulatory requirements. Monitoring includes an on-site initiation visit, regular on- and off-site visits during the recruitment phase and a close-out visit. Before the study start, the participating sites will be personally trained and introduced to all study specific procedures during the on-site initiation visits. After each visit, the monitor will prepare a report for the sponsor and a follow-up letter with findings and eventual necessary measures for the sites. All procedures will be pre-defined in the monitoring manual.

All planned substantial changes of the clinical trial need to be signed by the sponsor, the coordinating investigator, the biometrician and the clinical pharmacology consultant. According to §10 of the GCP ordinance (GCP-V), protocol amendments are submitted in writing to the responsible Ethics Committee and the national competent authority.

### **Statistical analysis plan**

#### Sample size estimation

The sample size calculation is based on the primary endpoint FACIT-F fatigue subscale. We assume that the FACIT-F fatigue subscale is approximately normally distributed. An increase in the FACIT-F fatigue subscale by three points was found to be a clinically relevant reduction of fatigue [19]. The assumed mean and standard deviation of the FACIT-F fatigue subscale are taken from the representative study of Jones et al. [4], which were 38.5 and 10.8, respectively. With a significance level of 0.05 and 80% power, 205 patients are needed in each group to detect a score difference of three or more points using a two-sample t-test for the mean difference, i.e. 410 patients are required in total. The number of patients to be randomized was calculated assuming a 10% drop-out rate. With these assumptions 500 CRC patients need to be screened and 456 eligible persons randomized to achieve the analyzable sample size of *n* = 410.

Given the annual number of overall 1400 eligible CRC patients reported by the participating three rehabilitation clinics in 2016, recruiting of 456 eligible stage I-III CRC patients should be feasible within 24 months.

### Statistical methods

All analyses will be done using SAS software version 9.4 or higher. Homogeneity of the treatment groups will be described by comparison of the demographic data and the baseline values of key variables. All statistical tests will have a two-sided significance level of 0.05. Besides, 95% confidence intervals will be estimated for all outcomes in the placebo and verum group.

The primary analysis will test the null hypothesis.

H_0_: The FACIT-F fatigue subscale at week 13–16 is the same in the two groups.

versus the alternative hypothesis.

H_1_: The FACIT-F fatigue subscale at week 13–16 is different in the two groups.

The primary endpoint FACIT-F fatigue subscale will be analyzed with an intention-to-treat approach. The intention-to-treat population will include all randomized study participants with data for the primary endpoint and who did not withdraw consent during the trial. A per-protocol analysis will be done additionally as a sensitivity analysis. The per-protocol population will exclude study participants who meet the following criteria:
Fatigue questionnaire missing at trial week 13–16Error in timing of collection of fatigue questionnaire at trial week 13–16After enrollment, it becomes evident that patient met exclusion criteria at time of recruitment or did not meet inclusion criteria.Incompliance to trial medication (defined as intake of less than 80% of capsules) unless treatment was terminated due to safety reasonsSelf-reported intake of vitamin D or vitamin D analogs in addition to the trial medication.Criteria for discontinuation of study medication were met but study medication intake was continued.

We will test on normal distribution for the outcome FACIT-F fatigue subscale with the Shapiro-Wilks test. If normal distribution can be assumed, the primary test statistic will be the two-sample t-test for the mean difference. If normal distribution cannot be assumed for the FACIT-F fatigue subscale, we will log-transform the FACIT-F fatigue subscale and test for normal distribution once more with the Shapiro-Wilks test. If normal distribution can neither be assumed for FACIT-F fatigue subscale nor log-transformed FACIT-F fatigue subscale, a Wilcoxon Rank-Sum test will be applied. In addition, appropriate 95% confidence intervals will be estimated for the FACIT-F fatigue subscale in the two groups and for the difference in FACIT-F fatigue subscale between the two groups.

A priori defined subgroup analyses will be conducted for groups defined by age (< 65 / ≥ 65 years), sex (male / female), CRC stage (I or II / III), 25(OH)D levels at screening (< 30 / ≥ 30 nmol/L), season at screening (Dec-Feb/Mar-Mai/Jun-Aug/Sept-Nov), BMI at screening (< 30 / ≥ 30 kg/m^2^), FACIT-F fatigue subscale at screening (≤ 34 / > 34 points), mild to moderate anemia at screening (hemoglobin 8–10 mg/dl / > 10 mg/dl), chemotherapy and/or radiotherapy in 9 months before screening (yes / no), chemotherapy and/or radiotherapy during trial (yes / no), geriatric depression scale (GDS-15) score at follow-up (< 5 / ≥ 5 points), insomnia at follow-up (EORTC QLQ-C30 insomnia item < 3 / ≥ 3 points), pain at follow-up (EORTC QLQ-C30 pain scale < 6 / ≥ 6 points), use of strong opioids (ATC codes N02AB03, N02AA01, N02AG01, N02AA51, N02AA03, N02AG04, N02AA53, N02AA05, N02AJ18, N02AJ19, N02AA55, N02AA56, N02AJ17, N02AX06, N02AE01, and N02AA25) at follow-up (yes / no), use of psycholeptics (ATC code N05) at follow-up (yes / no), and use of corticosteroids for systemic use (ATC code H02) at follow-up (yes / no).

In addition, a subgroup analysis will be conducted for study participants, who most likely profit from the vitamin D_3_ intervention because the following conditions apply combined (yes / no): No protocol deviations (patients did not withdraw consent during the trial, were adherent to the trial medication (defined as taking at least 80% of all capsules), and did not take vitamin D_3_ or vitamin D analogs in addition to the trial medication), FACIT-F fatigue subscale ≤34 at screening, and neither use of strong opioids nor psycholeptics at follow-up.

A mean difference ≥ 3 FACIT-F fatigue subscale points will be considered a clinically relevant difference [19].

Depending on the availability of future funding for genotyping of all randomized trial participants, further subgroup analyses are planned that stratify trial participants by genetic susceptibility for low 25(OH)D levels or cancer related fatigue [38, 39].

As a sensitivity analysis, a linear regression model will be carried out with FACIT-F fatigue subscale as the dependent variable and treatment group as the independent variable. The linear regression model will be adjusted for all variables named in the subgroup analysis while using some variables continuously instead of categorically (age, hemoglobin levels at screening, 25(OH)D levels at screening, BMI at screening, FACIT-F fatigue subscale at screening, insomnia scale at follow-up and pain scale at follow-up). If appropriate, missing covariate values will be imputed with multiple imputation.

All secondary endpoints with a continuous scale will be analyzed with the same statistical methods as described for the primary endpoint. All dichotomous secondary endpoints will be tested with a Chi^2^ test. AEs will be analyzed with descriptive statistics including frequencies of SAEs.

Lastly, the success of the personalized vitamin D_3_ intervention in raising the serum 25(OH)D level will be evaluated in the intervention group at trial day 12–21. Furthermore, the success of the maintenance dose to maintain sufficient vitamin D status in the intervention group will be evaluated in trial week 13–16. To be successful, the mean 25(OH)D levels in the group with personalized vitamin D_3_ intervention should be higher than 50 nmol/L. This translates into the following test hypotheses:
H_0_: Mean 25(OH)D_personalized intervention_ ≤ 50 nmol/LH_1_: Mean 25(OH)D_personalized intervention_ > 50 nmol/L

To test these hypotheses, we will conduct a one-sample t-test on the mean 25(OH)D levels at a one-sided significance level of 0.025. 25(OH)D levels may be log-transformed if this improves the approximation of a normal distribution (to be tested with a Shapiro-Wilks test).

*Exploratory sub-project: “Determinants of the achieved 25(OH)D levels by the personalized vitamin D*_*3*_*intervention”*

In the following, we describe the statistical methods of an observational sub-project for the secondary outcome “25(OH)D level”. This solely observational research project shall be addressed in those 228 VICTORIA trial participants who received the personalized vitamin D_3_ intervention and adhered to the trial medication (defined by taking at least 80% of the trial medication capsules), which will result in a final sample size *n* < 228. If 25(OH)D levels or log-transformed 25(OH)D levels are normally distributed (to be tested with a Shapiro-Wilks test), a linear regression model will be carried out with a continuous 25(OH)D level variable. In addition, a logistic regression model will be used with a dichotomized 25(OH)D level variable (< 50 nmol/L / ≥ 50 nmol/L) as the dependent variable.

Covariates for the linear and logistic regression model will be study center, age, sex, baseline 25(OH)D, compliance up to time of blood sampling, difference between exactly calculated and rounded supplied loading dose, number of days between last intake of trial medication and blood sampling, season at recruitment, baseline BMI, baseline waist circumference, baseline smoking, baseline physical activity, baseline physical functioning (EORTC QLQ-C30 subscale), baseline Charlson Comorbidity index, baseline frailty, baseline FACIT-F fatigue subscale, GDS-15 total score ≥ 5 points (at baseline), baseline anxiety (GAD-7 score), baseline pain (EORTC QLQ-C30 pain scale), CRC stage, time since CRC tumor surgery, stoma, concomitant use of vitamin D products (at follow-up), chemotherapy and/or radiotherapy in 9 months before trial (yes / no), chemotherapy and/or radiotherapy during trial (yes / no), concomitant use of laxatives (at baseline and/or follow-up), concomitant use of other drugs limiting vitamin D_3_ bioavailability at baseline and/or follow-up (phenytoin, barbiturates, systemic glucocorticoids, rifampicin, isoniazid, cholestyramine, orlistat, dactinomycin or systemic azole-antimycotics), nutritional vitamin D intake (at follow-up), appetite loss (at baseline and/or follow-up), sun exposure in last summer before baseline, skin type, solarium use in last 2 months before baseline, frequency of diarrhea (at baseline and/or follow-up), vitamin D binding protein levels and single nucleotide polymorphisms (SNPs) previously shown to be associated with low 25(OH)D levels. If appropriate, missing covariate values will be imputed with multiple imputation.

Mean 25(OH)D levels and proportions of study participants with 25(OH)D levels < 50 nmol/L will be presented distinctly for factors that were statistically significant (*p* < 0.05) determinants of achieved 25(OH)D levels.

The analyses will be carried out both for the 25(OH)D measurement from day 12–21 (end of loading dose consumption) and for the 25(OH)D measurement from week 13–16 (end of maintenance dose consumption).

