## Methods/Design

### **Study design**

The trial is conducted as a national multicenter, randomized, double-blind, and placebo-controlled phase III trial using a confirmatory approach. By applying a parallel group design, the participants are randomly assigned in a 1:1 ratio to either the intervention group or to the control group. Recruitment is carried out in three large German rehabilitation clinics and is assumed to take approximately 24 months. The list of trial sites can be obtained from the German Clinical Trials Register (DRKS00019907).

The trial protocol and this manuscript have been developed in line with the Standard Protocol Items: Recommendations for Interventional Trials (SPIRIT) guideline [17].

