**Fig. 1 Fig1:**
[figure not shown]
Overview of the study flow. Abbreviations: *EORTC QLQ-FA12* European Organization for Research and Treatment of Cancer – Cancer related Fatigue; *EORTC QLQ-C30* European Organization for Research and Treatment of Cancer – Core Quality of life questionnaire with 30 items; *FACIT-F* Functional Assessment of Chronic Illness Therapy-Fatigue; *FACIT-F FWB* Functional Assessment of Chronic Illness Therapy-Fatigue – Functional Well-being; *GDS-15* Geriatric Depression Scale with 15 items; *UICC* Union for International Cancer Control

In total, 456 eligible CRC patients are being randomized in order to analyze 410 for the primary endpoint after an expected drop-out rate of 10%. The trial schedule is presented in Table 3.

**Table 3 Tab3:** Detailed schedule of all observations to be performed during the clinical trial

Procedure	Screening Visit for eligibility	Visit 1 Start of treatment	Visit 2 End of rehabilitation	Collection of data via questionnaire/ phone and blood/urine sampling by GP
Rehabilitation clinic	Admission	–	Discharge	–
Time-point of data assessment	–	Day 1	Day 12–21	Week 13–16
Planned doses of vitamin D_3_ per day	–	Individualized initial dose (20,000 or 40,000 IU, followed by 2000 IU per day) for day 1–11	Maintenance dose of 2000 IU per day for day 12–21	–
Inclusion/exclusion criteria	●	●		
Written informed consent	●			
Randomization		●		
Trial medication intake		●	●	
Subject diary regarding days of drug administration		●	●	
Physical examination (weight, height, waist circumference)	●			
Urinary pregnancy test for women of childbearing potential	●			
Assessment of CRC treatment	●			●
Concomitant diseases / Medical history	●			
Concomitant medication	●			●
Query about concomitant use of vitamin D_3_ or vitamin D analogs in self-medication in addition to trial medication				●
Fatigue	●			●
Functional well-being, QoL, infection frequency, and depression	●			●
Blood sampling for biomarker efficacy and safety endpoints	●		●	●
Urine sampling for safety endpoints	●		●	●
(S)AE recording and protocol deviations		●	●	●

Abbreviations: *CRC* colorectal cancer; *GP* general practitioner; *QoL* Quality of life; *SAE* Serious adverse event

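### The primary set labelled intention-to-treat is a complete-case set, and no stated fatigue analysis includes the roughly 10% of randomized patients expected to lack the outcome

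*Protocol article*

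**What the plan says.** The Study design section describes a "phase III trial using a confirmatory approach". Under Statistical methods, "The primary endpoint FACIT-F fatigue subscale will be analyzed with an intention-to-treat approach", and the set is then defined: "The intention-to-treat population will include all randomized study participants with data for the primary endpoint and who did not withdraw consent during the trial". The test is applied to observed scores: "If normal distribution can be assumed, the primary test statistic will be the two-sample t-test for the mean difference". The fallbacks are a log transformation and then a Wilcoxon rank-sum test.

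Two sensitivity analyses are stated:
- A per-protocol analysis. Its exclusion list starts with a missing week 13–16 fatigue questionnaire.
- A linear regression of the fatigue score on treatment group, adjusted for all the subgroup variables, including screening FACIT-F. Here, if appropriate, "missing covariate values will be imputed with multiple imputation". Imputation of the outcome is not mentioned.

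The Study flow section plans for the loss: "456 eligible CRC patients are being randomized in order to analyze 410 for the primary endpoint", with an expected drop-out of 10%. The paragraph on weeks 13 to 16 describes efforts to limit it: repeated contact by mail and finally by phone, and a payment. Table 3 shows fatigue assessed only at screening and at weeks 13–16.

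**The concern.** Intention-to-treat normally means that everyone randomized counts in the arm to which they were allocated. Here, membership depends on returning a questionnaire and on not withdrawing consent, and treatment or its consequences could influence either. The second condition also removes anyone who supplied a week 13–16 score and then withdrew.

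Randomization protects the comparison of all 456 patients. It does not automatically protect the comparison of the roughly 410 who remain. If patients without a score would have been more fatigued than completers, and if their share differs by arm, the observed difference is shifted. More loss in the vitamin D arm would flatter vitamin D; more loss in the placebo arm would count against it.

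Both stated sensitivity analyses also work only on patients with an observed score. Agreement between them and the primary result would therefore say little about loss that depends on the unobserved score. A reader who sees the intention-to-treat label would assume more protection than the analysis gives.

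**Working it through.** **Inputs from the protocol article.** Target difference 3 points, SD 10.8, 80% power, 205 per group, 410 analyzable, 10% drop-out and 456 randomized (Sample size estimation); two-sided level 0.05 (Statistical methods); 1:1 allocation (Study design).

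**Inputs that are assumptions.** The loss in each arm (m_V for vitamin D, m_P for placebo) and the gap d, meaning how many points lower the missing patients would have scored than completers. The documents give none of these.

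**Step 1: the plan's own figures.**
- Normal approximation: n = 2 × (1.96 + 0.842)² × 10.8² / 3² ≈ 204 per group. The exact t-test calculation gives 205 (power 80.1%; 204 gives 79.9%).
- 2 × 205 = 410, and 410 / 0.90 = 455.6, rounded up to 456.

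The stated 205, 410 and 456 all reproduce.

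**Step 2: the planned exclusion.** 456 − 410 = 46, and 46 / 456 = 10.1%.

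**Step 3: bias of the completer difference.** The completer mean in an arm exceeds the mean of all randomized patients in that arm by m × d. With the same d in both arms, the bias in the difference is d × (m_V − m_P). Its size is:

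| Assumed loss, one arm vs the other | d = 5 | d = 10 |
|---|---|---|
| 10% vs 10% | 0 | 0 |
| 8% vs 12% | 5 × 0.04 = 0.20 | 10 × 0.04 = 0.40 |
| 5% vs 15% | 5 × 0.10 = 0.50 | 10 × 0.10 = 1.00 |

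The largest entry, 1.00, is one third of the 3-point target.

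**Step 4: scale against precision.** SE = 10.8 × √(2/205) = 1.07. If there were no true effect, the two-sided type I error of 5% would become about 5.4% at a bias of 0.20, about 7.6% at 0.50 and about 15.5% at 1.00.

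**Step 5: a tipping point.** The smallest significant difference is about 1.966 × 1.067 = 2.10. An observed difference of exactly 3.0 loses significance if the shift reaches 3.0 − 2.10 = 0.90. If only the missing 10% of the vitamin D arm are penalized, and the SE is held fixed, that needs 0.90 / 0.10 ≈ 9 points.

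**Step 6: which stated analysis includes a patient without a week 13–16 score?**
- Primary test: none, by definition of the set.
- Per-protocol: none. A missing questionnaire is listed as an exclusion, although the primary set has already removed those patients. This redundancy changes no result.
- Adjusted regression: none. The outcome must be observed, and only covariates are imputed.

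**The case against.** **The article is condensed.** Imputation models and tipping-point analyses are commonly left to a full protocol or SAP, which are not shown. That stands, and the absence of such detail is not the point. The point is the definition of the primary set, which the article fixes and which excludes patients without an outcome.

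**The adjusted regression offers some protection.** This stands in part. If loss depends only on arm and on modelled baseline variables such as screening FACIT-F, a correctly specified complete-case regression is unbiased, and imputing the outcome from those same variables adds little. A contrast with the t-test could then show baseline-related loss. A reader might infer that nothing planned could reveal a problem; the document does not support that. But the model also adjusts for follow-up variables (depression score, insomnia, pain, treatment during the trial, drug use). Treatment may affect these, which weakens the model as a check. It cannot address loss that depends on the unobserved score.

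**No passage shows loss that differs by arm.** This stands. One might infer that patients taken off medication for laboratory reasons will not return the questionnaire. The document does not say so: stopping medication is not leaving follow-up. Patients who stop or do not comply stay in the primary set if they answer and keep consent, so it is not an on-treatment analysis. Routine unblinding of a participant comes only after the end of that participant's trial is reported. Repeated contact and payment should keep loss low.

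**The larger figures need a threefold imbalance.** This also stands. The 5% versus 15% split is illustrative.

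**Conclusion.** The point holds as one of labelling and of missing protection. The confirmatory analysis is a complete-case analysis under an intention-to-treat name. It plans to leave out about 46 of 456 patients, and no stated analysis of fatigue includes participants with missing outcomes.

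Bias is possible, not established. It is zero with equal loss and a common gap, about 0.2 points under a mild assumed imbalance, and 0.5 to 1.0 points under a strong one, against a 3-point target and an SE of about 1.07. These sizes rest on assumed loss rates and gaps.

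It would be wrong to infer that the trial is underpowered on this account: the sample size reproduces and already allows for 10% drop-out. That allowance protects power, not validity. Confidence is high for the mislabelling and low for any particular size of bias. This should be fixed, but it does not by itself invalidate the plan.

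**What to change.** - Define intention-to-treat as all randomized participants in their allocated arm. Keep data collected before withdrawal where consent permits, including any week 13–16 score already supplied.
- Retain the present set, under the name complete-case.
- Add an analysis with multiple imputation of the missing week 13–16 FACIT-F score, using arm, centre, screening FACIT-F and other baseline data already collected. Leave follow-up covariates that treatment may affect out of the treatment comparison.
- Add a delta-adjusted sensitivity analysis that lowers the imputed scores by a range of points, separately by arm, and reports where the conclusion changes. This is the part that addresses loss related to the unobserved score.
- Report the number and, where volunteered, the reasons for missing outcomes by arm.

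If the full SAP already contains the imputation and delta analyses, only the definition and the label need to change. The primary test can stay as it is for this purpose, and the required sample size is unchanged. If all 456 outcomes were observed, power for 3 points would be 84.1%; imputed outcomes do not restore that in full.

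The cost is modest programming and an amendment. If the change counts as substantial, the Quality control and assurance section requires several signatures and submission to the Ethics Committee and the competent authority. No new data are needed. Because participants are unblinded individually while the trial runs, the rule should be fixed before outcome data accumulate.

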### Intervention

For the verum, 20,000 IU (Dekristol® 20,000 I.E., Mibe GmbH Arzneimittel) or 2000 IU colecalciferol (two tablets Dekristol® 1000 I.E., Mibe Arzneimittel GmbH) are encapsulated and filled up with a mixture of mannitol and colloidal silicon dioxide (Füllstoff DAC). The placebo consists solely of the hard gelatine capsules with filler. To ensure blinding, verum and placebo capsules are indistinguishable regarding appearance, quantity, weight, and packaging.

Patients, who have consented to participate in the trial, are randomly allocated to either vitamin D_3_ or placebo for a total of 12 weeks (84 days).

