#### *Intervention arm*

The vitamin D_3_ treatment consists of a personalized loading dose, followed by a daily maintenance dose of 2000 IU. Several clinical trials have highlighted that 25(OH)D levels, achieved by vitamin D_3_ intake, strongly depend on a person’s 25(OH)D level and weight at baseline [29–31]. In order to provide the trial participants with a sufficient vitamin D_3_ dose, an equation to calculate individual loading doses is applied. The equation includes the baseline 25(OH)D level and body mass index (BMI) [31]:

Loading dose = 165 * BMI [kg/m^2^] * (70 – baseline 25(OH)D level [nmol/L]).

The equation by Jansen et al. was developed to increase 25(OH)D levels to 80 nmol/L, which is slightly above the generally accepted optimal level of 75 nmol/L [32]. In order to avoid non-physiological high doses of vitamin D_3_, the loading dose will be distributed in daily doses of 20,000 IU, which resembles the maximum amount of vitamin D_3_ that can be naturally produced in the skin by sunbathing in a swimsuit on a summer day [33]. The reasons for this are not safety concerns but mechanistic considerations regarding the vitamin D_3_ metabolism: Unbound vitamin D_3_ in the serum is of major importance for effective vitamin D activity [34, 35]. Its bioavailability in turn is higher when doses are given on a daily basis while avoiding single high doses [34, 35].

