However, if the total personalized vitamin D_3_ loading dose of a participant is exceptionally high, 2 × 20,000 IU/day will be administered at the beginning to ensure that the entire vitamin D_3_ loading dose is administered within the first 11 days, while the patient is still in the rehabilitation clinic (for safety reasons). Accordingly, the maximum achievable loading dose of vitamin D_3_ is fixed at 420,000 IU over 11 days. This dose would only be necessary for an individual with a 25(OH)D level of 5 nmol/L (lowest expected baseline level) and a BMI of 40 kg/m^2^ (maximum possible BMI in this trial since patients with BMI > 40 kg/m^2^ are excluded). After administrating the last loading dose capsule, patients will continue with the maintenance dose on the next day until the end of the intervention (day 84). The daily maintenance dose (2000 IU) corresponds to the upper limit of the Endocrine Society’s recommendations for adults at high risk for vitamin D deficiency. It was chosen on the assumption that early stage CRC patients who only recently underwent rehabilitation have a higher turnover of vitamin D metabolites than individuals from the general population [32]. Depending on the loading dose, overall doses will range between 168,000 and 566,000 IU vitamin D_3_ taken over 84 days.

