#### *Compliance*

To ensure a high adherence to the trial protocol, all patients are thoroughly instructed orally at regular visits and in writing via the patient information documents. Daily intake of study medication and potential adverse events (AEs) are recorded in the patient diary. The participant can agree to receive a weekly SMS, reminding them to take their medication and fill in the diary. It will be allowed to take forgotten maintenance doses of the week on the day of the SMS reminder.

The investigator documents the supply of the trial medication as well as the return of unused loading dose capsules and/or empty packages. The coordinating center (Division of Clinical Epidemiology and Aging Research at the German Cancer Research Center, Heidelberg) keeps records of the return of unused maintenance dose capsules and/or empty packages. Intake of less than 80% of the trial medication will be defined as incompliance.

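### The 80%-of-capsules adherence rule sets no minimum for the loading phase, so with up to 18 loading capsules a patient who takes none of them can still count as compliant

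*Protocol article*

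**What the plan says.** Adherence is defined in four places in the protocol article:

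- Compliance section, with no unit: "Intake of less than 80% of the trial medication will be defined as incompliance".
- Statistical methods, per-protocol exclusions: "Incompliance to trial medication (defined as intake of less than 80% of capsules", with an exception where treatment was ended for safety reasons.
- Statistical methods, combined subgroup of patients expected to profit most: "defined as taking at least 80% of all capsules".
- Exploratory sub-project on determinants of achieved 25(OH)D: participants who "adhered to the trial medication (defined by taking at least 80% of the trial medication capsules".

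The capsules are of two kinds. The Intervention section describes one with 20,000 IU and another with a tenth of that: "or 2000 IU colecalciferol (two tablets Dekristol® 1000 I.E., Mibe Arzneimittel GmbH) are encapsulated". The number of loading capsules follows from "Loading dose = 165 * BMI [kg/m^2^] * (70 – baseline 25(OH)D level [nmol/L", and "the maximum achievable loading dose of vitamin D_3_ is fixed at 420,000 IU over 11 days". Maintenance starts the day after the last loading capsule and runs to day 84. Placebo follows the same schedule.

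The per-protocol analysis is a sensitivity analysis to the intention-to-treat primary analysis. None of these definitions sets a separate minimum for the loading phase or weights capsules by content.

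**The concern.** The personalised loading dose is what the article presents as the trial's novel element. An adherence rule meant to identify patients who received the regimen should notice when that element is missing. Maintenance capsules far outnumber loading capsules, so a count over all capsules is dominated by maintenance and can be passed with little or no loading.

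Three sets are at stake: the per-protocol set, the combined subgroup and the sub-project population. Verum patients without their loading dose would stay in the first two and, if loading contributes to the effect, pull the difference towards zero. In the sub-project, a low 25(OH)D at day 12–21 could reflect capsules not taken rather than the determinants under study.

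The sub-project has a further mismatch. It analyses day 12–21 and week 13–16 separately but admits patients by one count over all trial capsules. Maintenance capsules missed after the first blood sample can therefore remove a patient from the day 12–21 analysis.

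**Working it through.** **Inputs.** Capsule contents of 20,000 and 2,000 IU (Intervention); loading formula, 11-day limit, 420,000 IU maximum and 84 days (Intervention arm); 80% threshold (Compliance, Statistical methods). Assumed: whole loading capsules, one loading capsule per day unless doubling is needed to finish within 11 days, and one maintenance capsule per day.

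**Formulas.** With L loading capsules:
- maintenance capsules M = 84 − min(L, 11)
- planned IU = 20,000 × L + 2,000 × M
- with no loading capsule and all maintenance capsules taken, capsule share = M/(L + M) and IU share = 2,000 × M / planned IU

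**The plan's own figure first.** At BMI 40 and 25(OH)D 5 nmol/L the formula gives 165 × 40 × 65 = 429,000 IU, which is 21 whole capsules or 420,000 IU. Then M = 84 − 11 = 73, and 420,000 + 73 × 2,000 = 566,000 IU. This is the stated maximum overall dose, so the capsule model reproduces it.

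**Illustrative patient (assumed BMI 27, 25(OH)D 25 nmol/L).** 165 × 27 × 45 = 200,475 IU, about 10 loading capsules. M = 74, total 84 capsules, planned 200,000 + 148,000 = 348,000 IU.

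**No loading capsule taken, all maintenance capsules taken:**

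| L | M | Capsule share | IU share | Counted as |
|---|---|---|---|---|
| 3 | 81 | 81/84 = 96.4% | 162,000/222,000 = 73.0% | compliant |
| 10 | 74 | 74/84 = 88.1% | 148,000/348,000 = 42.5% | compliant |
| 18 | 73 | 73/91 = 80.2% | 146,000/506,000 = 28.9% | compliant |
| 19 | 73 | 73/92 = 79.3% | 146,000/526,000 = 27.8% | incompliant |
| 21 | 73 | 73/94 = 77.7% | 146,000/566,000 = 25.8% | incompliant |

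The row with L = 3 corresponds to an assumed BMI of 18.5 at the highest season-adapted cut-off of 50 nmol/L: 165 × 18.5 × 20 = 61,050 IU.

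**Maximum regimen, partial omission.** Missing 18 of 21 loading capsules leaves 3 + 73 = 76 of 94 capsules, or 80.9%. The IU taken are 60,000 + 146,000 = 206,000 of 566,000, or 36.4%. This patient counts as compliant.

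**Effect of a two-part rule.** Anyone with at least 0.8 × L loading capsules and at least 0.8 × M maintenance capsules has at least 0.8 × (L + M) overall. The new set is therefore contained in the present one.

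**The case against.** The strongest case against is that the harmful pattern should be rare. Loading is taken as an inpatient under medical supervision, and empty loading packages and leftovers are checked at visit 2. The sub-project also adjusts for compliance up to the time of blood sampling, which at day 12–21 reflects mainly the loading phase. All of this stands and lowers the weight of the point. It does not remove it, because the visit 2 check feeds no separate per-protocol criterion and a covariate does not decide who enters the sub-project.

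A reader might also infer that the rule errs in the other direction by excluding patients who took about 90% of the IU. With 10 + 74 capsules, missing 17 maintenance capsules leaves 67/84 = 79.8% of capsules but 314,000/348,000 = 90.2% of the IU. The documents do not support calling that an error. Daily maintenance to day 84 is part of the assigned regimen and is evaluated in its own right at week 13–16, when the primary endpoint is also measured. A patient with 57/74 = 77% of maintenance is genuinely non-adherent, and the remedy below still excludes this patient.

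Nor can it be said that the loading dose is usually more than half of the total. That holds from 8 loading capsules (160,000 of 312,000 IU) but not at 7 (140,000 of 294,000 IU, or 47.6%), and the article gives no joint distribution of BMI and 25(OH)D for the trial population.

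The Compliance section's missing unit is a small matter, since the other three definitions all say capsules. It needs alignment only.

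**Conclusion.** The concern holds in a limited form and is minor. For regimens of up to 18 loading capsules (360,000 IU), a patient who takes no loading capsule but all maintenance capsules counts as compliant, with an IU share between 73.0% (3 loading capsules) and 28.9% (18). At 19 to 21 loading capsules complete omission is caught, but at 21 the omission of 18 is not.

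The result rests on whole 20,000 IU capsules, one maintenance capsule per day and, for the worked patient, an assumed BMI and 25(OH)D. How many patients would be affected cannot be derived from the article. Only the per-protocol sensitivity analysis, one subgroup and the exploratory sub-project depend on the rule. It would be wrong to infer that the primary intention-to-treat result is at risk.

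**What to change.** Define adherence as intake of at least 80% of the loading capsules and at least 80% of the maintenance capsules. Count by capsule type, identically for verum and placebo, because placebo capsules contain no IU. Use this one definition in the Compliance section, the per-protocol exclusions (keeping the existing safety exception), the combined subgroup and the sub-project. For the sub-project's day 12–21 analysis, count only capsules due up to that blood sample. Settle the wording before the planned interim analyses, since they include the sub-project.

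No new data are needed: loading returns are documented by the investigator, maintenance returns by the coordinating center, and daily intake in the patient diary. The cost is that the per-protocol set can only stay equal or become slightly smaller. With few loading capsules the new criterion is strict: with 3 or 4, one missed capsule gives 2/3 = 66.7% or 3/4 = 75% and fails. The plan should say that this is intended.
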